### Relevant concomitant care permitted or prohibited during the trial

The aim of this study is to examine effectiveness of BFO when delivered via a telehealth approach as an adjunct to standard treatment, therefore, both interventional and control groups will receive standard treatment. Existing standard treatment utilized by the participating NHS Trust may be variable, therefore it is expected that there will be a degree of heterogeneity within each of the study groups—this heterogeneity will be captured in the participant’s source data. Treatments usually available in outpatient SUD services include standard low-intensity interventions such as motivational and engagement tools to reduce substance use—more intensive psychological therapies such as CBTs may also be delivered. Not all standard treatment sessions will be delivered in-person—some participants may receive sessions via telephone calls rather than in-person sessions in the service. Standard treatment sessions will likely have a duration range of 30–60 min and will take place once or twice a week for eight-weeks. Medications may also be prescribed, including substitute medications such suboxone, buprenorphine etc. and also psychotropic medications such as anti-depressants, anti-anxiolytics etc.

### Outcomes

Outcomes data will be collected via self-report, with participants completing an online assessment containing a series of standardized psychometric measures at Baseline, End of Treatment, and 3-month and 6-month follow up timepoints. Additionally, engagement data (time spent accessing the program, number of BCTs engaged with) will be collected automatically via the BFO backend database for those participants in the interventional arm.

The primary outcome will be self-reported substance use compared to baseline following treatment completion, and at three and six-months follow-up, which will be measured using the following questions:Weekly use of primary problem substance (i.e., ‘How many days in the past week did you use [primary substance]?’‘How much [primary substance] did you use each day?’)

Secondary outcomes will be measured at corresponding time points using the following standardized measures:Severity of Dependence Scale (SDS) [37, 38]: A five-item scale measuring severity of substance dependence—internal reliability: α = 0.81–0.90; test–retest reliability ICC = 0.89.Patient Health Questionnaire-4 (PHQ-4) [39]: A four-item scale that measures severity of depression and anxiety—internal reliability, α = 0.81.Five items (1, 2, 17, 18, 20) from the World Health Organization Quality of Life scale (WHOQoL-BREF) [40]—internal reliability of these five items, α = 0.84.Recovery Progression Measure (RPM) [34, 35]: A 36-item scale measuring functioning in six biopsychosocial domains functioning that are implicated in all SUDs and recovery from SUDs—internal consistency, α = 0.89; test–retest reliability, ICC = 0.73.

### Randomization

Randomization will occur at the level of individual participants using a random allocation sequence via the Research Randomizer [41]. Sequentially numbered opaque sealed envelopes containing the group that each participant will be allocated to will be prepared prior to commencement of the study. Treatment allocation sequences will be generated by a member of the research team and disseminated to the participating organization via sealed opaque envelope. Participants will be enrolled into the study and subsequently assigned to a treatment condition by a member of the research team at the participating organization. Because this study is a non-pharmaceutical study open-label study, no blinding is required—however, the study statistician will be blinded to treatment allocation when analyzing study data. Participants will be identified by a participant identification or randomization number only on all trial documentation, except for informed consent documents. Where there is a need for Sponsor personnel to verify trial documentation against medical records or other data sources containing identifiable information, this will be permitted by the research site, provided that subject confidentiality is maintained in accordance with local regulations and requirements.

### Adverse event reporting

Historically, the recording and reporting of adverse events (AEs) has been inconsistent and poorly defined in psychological and behavioral intervention randomized controlled trials (RCTs) [42]. One factor that may contribute to the under-reporting of adverse events in such trials is the assumption that AEs are purely medical in nature and are thus unlikely to be caused by non-medicinal interventions. However, psychological and behavioral interventions may cause psychosocial harms [43]. Behavioral interventions requiring individuals to reflect on their substance use may cause non-medical adverse events, or ‘social AEs’ [44] such as involvement with law enforcement, safeguarding referrals, perpetration of domestic abuse, and involvement with social services. These alternative harms are often poorly documented in the context of RCTs [45], yet may prove vital when assessing the risk–benefit profile of an intervention. In addition to this, the use of computers to deliver behavioral interventions may mean an increased incidence of technology-related medical adverse events, such as increased incidences of headaches and migraines, which may feasibly be medical consequences of a non-medicinal intervention.

Both medical and social AEs will be documented and monitored throughout the course of the study for both groups. Adverse event data will be obtained via retrospective review of participants’ medical notes—events occurring between randomization and the 6-month follow-up timepoint will be recorded at the time of each participant’s completion of the study.

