**Fig. 1 Fig1:**
[figure not shown]
The Lifestyle Balance Model

Based on RPM scores, each of the domains of the LBM are colored either green, amber, or red, indicating respectively, ‘little’, ‘moderate’ or ‘significant’ impairment. Tailoring advice then guides the user to complete clinical content of the program that is able to address the domains of their functioning in the LBM where they may be experiencing the greatest levels of impairment (amber and red domains of the LBM). Individuals are able to address these domains of functioning by completing the 12 main BCTs included in the program (see Table 1). Every two-weeks BFO prompts each user to complete a mandatory ‘Progress Check’ assessment, which is comprised of the same items as the baseline assessment. Alongside providing access to the BFO program, participants will receive fortnightly 15–20 min recovery check-in telephone calls from the SUD service—a total of four telephone calls during the treatment period. Phone calls will include questions relating to the participant’s understanding and perception of the content of BFO, their ability to practice and rehearse the skills they are learning from the program, and support needs.

**Table Tab1:** The 'behavioral change techniques' (BCTs) contained within Breaking Free Online

Content in Breaking Free Online	Description of strategy	Therapeutic approaches underpinning strategies	BCT taxonomy (V1) techniques (number in taxonomy)
Baseline and progress check assessments	Monitor behavior to provide feedback about progress towards goals; Encourage new behaviors via positive feedback	Goal setting; self-monitoring	Self-monitoring of behavior (2.3); Feedback on outcome(s) of behavior (2.7)
Lifestyle Balance Model	Generic formulation; Idiosyncratic formulation; Personalized feedback; Case formulation—understand the links between situations, thoughts, emotions, behaviors, physical sensations, and lifestyle	Node-link mapping (International Treatment Effectiveness Project (ITEP); Cognitive-behavioral therapy (CBT)	Information about antecedents (4.2); Information about health consequences (5.1); Salience of consequences (5.2); Information about social and environmental consequences (5.3); Information about emotional consequences (5.6)

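### Adverse events come only from medical notes, and no participant is asked about them, so harms the protocol itself expects may go unrecorded

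*Protocol article*

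**What the plan says.** All of this is in the protocol article. The section Adverse event reporting opens with a case for taking non-medical harms seriously. It lists "involvement with law enforcement, safeguarding referrals, perpetration of domestic abuse, and involvement with social services" as social adverse events, says that such harms are seldom well recorded in randomized trials, and says that they may be essential to weighing risk against benefit. It adds that computer delivery may bring technology-related medical events, such as "increased incidences of headaches and migraines".

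The procedure follows in two sentences. The first is a commitment: "Both medical and social AEs will be documented and monitored throughout the course of the study for both groups". The second gives the source, "Adverse event data will be obtained via retrospective review of participants’ medical notes", and the timing: "events occurring between randomization and the 6-month follow-up timepoint will be recorded at the time of each participant’s completion of the study".

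Provisions for post-trial care makes the offer of BFO to all participants conditional on no negative effects or serious adverse events being found to be associated with it.

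**The concern.** The method does not match the reason given for it. A notes review finds only what a participant mentioned or a clinician learned, and what was then written down. Safeguarding referrals and social-services involvement often generate a record. A headache after screen use, a police contact or an episode of domestic abuse need not. The protocol names all of these as events of interest, yet no stated procedure asks a participant about any of them.

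There is also an imbalance between arms. The BFO arm receives fortnightly "recovery check-in telephone calls from the SUD service", and the control arm does not. The calls are not described as AE collection, but a service that speaks to participants more often has more chances to write something in the notes.

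What is at stake is the safety conclusion. The primary outcome is not affected. Under-capture in both arms makes it easier to find no harm. Extra capture in the BFO arm pushes the comparison the other way. A reader of the results could not separate either effect from a true difference.

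**Working it through.** **1. Is any other stated contact an AE source?**

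| Place in the protocol article | What it covers | Arms | AE capture stated? |
|---|---|---|---|
| Interventions: fortnightly Progress Check | "which is comprised of the same items as the baseline assessment", i.e. substance use, dependence and functioning | BFO only | No |
| Interventions: four calls | BFO content, skills practice, support needs | BFO only | No |
| Outcomes: "participants completing an online assessment containing a series of standardized psychometric measures at Baseline, End of Treatment, and 3-month and 6-month follow up timepoints" | Substance use, SDS, PHQ-4, five WHOQoL-BREF items, RPM | Both | No |
| Relevant concomitant care: standard sessions | Treatment | Both | No, but the main route into the notes |
| Criteria for discontinuing or modifying allocated interventions | Changes to treatment are documented, including changes to standard treatment made because of harms | Both | No; it records changes, not events |
| Data analysis and management: monitoring visits | Data monitoring | Trial level | No |

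The notes review is the only stated AE source.

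**2. How much extra contact does the BFO arm have?**

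- Standard sessions: likely once or twice a week for eight weeks, 30–60 minutes each. That is 8 to 16 contacts, and 8 × 30 = 240 to 16 × 60 = 960 minutes.
- Calls: 4 of 15–20 minutes, so 4 × 15 = 60 to 4 × 20 = 80 minutes.
- Extra contacts: 4/16 = 25% to 4/8 = 50%.
- Extra minutes: 60/960 = 6% to 80/240 = 33%.

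**3. What does imperfect capture do?** Let p_B and p_C be the true event risks in the BFO and control arms, and c_B and c_C the probabilities that an event reaches the notes.

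- Equal capture (c_B = c_C = c): observed difference = c × (p_B − p_C). A true excess shrinks in proportion to c.
- Unequal capture: observed ratio = (p_B/p_C) × (c_B/c_C). If the calls raise c_B above c_C, BFO looks worse than it is.

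The protocol gives no value for c, so the bias has a form and a direction but no size.

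**4. When is the record made?** Inputs: BFO ends on day 8 × 7 = 56, and a month is 365.25/12 = 30.44 days.

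The plan's own duration comes first. Eight weeks plus six months is 56/30.44 + 6 = 7.8 months. Participant timeline gives about ten months, so roughly 10 − 7.8 = 2.2 months are unexplained and the figure is not reproduced.

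Lag from the end of BFO to completion:

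- Six months from the end of treatment: 6 × 30.44/7 = **26.1 weeks**. The interim analysis text in Data analysis and management counts follow-up from treatment completion, so this is the best-supported reading.
- Six months from randomization: (182.6 − 56)/7 = 18.1 weeks. This is the most lenient reading and conflicts with that text.
- Ten months from randomization: (304.4 − 56)/7 = 35.5 weeks. This is an outer reading, because consent and eligibility precede randomization and may use part of the ten months.

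On the best-supported reading, completion is on day 56 + 182.6 = 238.6. An event on day 7 is recorded (238.6 − 7)/7 = 33.1 weeks later. With a week-8 extraction it would be recorded (56 − 7)/7 = 7.0 weeks later, a gain of 26.1 weeks.

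**The case against.** The strongest reply is that the procedure is coherent and treats the arms alike. Both arms are likely to be seen once or twice a week during treatment, so clinicians can write down events as they occur, and the trial extracts them later over a defined window. Clinicians can act on harms, and treatment modifications are documented. A notes review does not depend on returned questionnaires, which matters in a trial that allows for 50% attrition. Serious-event reporting may sit in the full protocol, which is not shown.

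Most of this stands, and it rules out three stronger readings that a reader might infer:

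- **That the two procedural sentences contradict each other.** They do not. Documentation by clinicians throughout, with later extraction by the trial, satisfies both.
- **That the trial is blind to harm during BFO exposure.** The document does not support this. Clinicians may see and act on events, and separate serious-event reporting may exist. Nor would a week-8 review detect a signal within that participant's own eight weeks.
- **That early finishers could be offered BFO before other participants' events are recorded.** The condition in Provisions for post-trial care reads most naturally as a trial-level conclusion. No earlier offer to individuals is stated.

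The reply does not answer the point about ascertainment. Frequent sessions help only if events are raised and written down, and no stated procedure asks about them. The same review method in both arms does not ensure equal capture when one arm has four more service contacts. Some named harms, such as safeguarding referrals, probably are recorded well, so the gap concerns part of the list and not all of it.

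**Conclusion.** The concern holds as a weakness in how harms are ascertained. The stated AE source is medical notes alone, reviewed at completion, for a set of harms that includes social events the protocol calls poorly documented and minor technology-related events that a participant may never mention. With four calls in one arm only, 25% to 50% more contacts over the treatment period if standard sessions run as expected, capture may also differ between arms. A finding of no negative effects would rest on weak evidence.

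The number of missed events cannot be estimated, because no capture or event rate is given. Differential noting because of the calls is plausible but not shown. The delay of about 26 weeks after BFO ends assumes that follow-up runs from treatment completion; 18 and 35 weeks are the outer readings. That completion is the only review point is inferred from the stated timing. For participants who withdraw, the article does not define completion, so their lag may be shorter. The delay is secondary; the main point is that participants are not asked.

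**What to change.** In Adverse event reporting:

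1. Add the same short set of medical and social AE questions for both arms to the end-of-treatment, three-month and six-month assessments. Each set should ask about events since the previous assessment and include headaches or migraines, police contact, domestic abuse, safeguarding and social services.
2. Keep the notes review for both arms.
3. Tag each event by source. Compare arms on sources common to both, and list separately any event known only through a BFO check-in call.
4. Optionally, add a notes extraction at week 8 in both arms. This gives a trial-level record about 26 weeks sooner, but not detection during that participant's exposure.

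**Cost.** Items 1 to 3 add a few questions to assessments already scheduled, plus one source field per event. Item 4 adds at most 183 reviews (the number to be recruited and screened, so an upper limit). At an assumed 10 to 20 minutes each, that is 183 × 10/60 = 30.5 to 183 × 20/60 = 61 hours.

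**Downside.** Self-reports come from unblinded participants and will be missing where assessments are not returned. For that reason the two sources should be reported side by side, with the notes review still available for both arms.

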### Criteria for discontinuing or modifying allocated interventions

Participants may be discontinued from BFO or standard treatment interventions at their own request at any point during the study. Additionally, participants’ standard treatment may be modified at the discretion of the Principal Investigator and clinical team at the participating site in response to worsening health status, or in response to perceived or actual harms resulting from their health status. Any discontinuation or modification of allocated interventions will be documented appropriately.

### Provisions for post-trial care

All patients will be returned to standard care within the participating Trust after inclusion, facilitated by the Trust’s research team and site PI. If no negative effects or serious adverse events are found to be associated with BFO, all participants, regardless of treatment allocation during the study, will be offered access to the program after trial inclusion.

### Participant timeline

Both groups will complete a period of eight-weeks of SUD treatment, of either (i) BFO plus standard treatment, or (ii) standard treatment only. The assessment battery will then be administered to all participants, via an online or hardcopy version, at the end of the eight-week treatment period, and at three and six-months follow-up. Each participant will take part in the study for a total of approximately 10-months. Please see Fig. 2 for a full description of the study timeline and all participant activities, including treatment schedule and assessment timepoints. 

**Fig. 2 Fig2:**
[figure not shown]
Study timeline and participant activity schedule

### Data analysis and management

Data will be analyzed using SPSS® Version 26.0 (or later). The principal data analytical strategy will be a repeated measures analysis of variance (ANOVA) in order to make a longitudinal comparison of treatment groups for the primary and secondary outcomes along the follow-up time points. The appropriate 95% confidence interval will be applied. The main statistical analyses will be conducted by the Chief Investigator with specialist statistical support from co-investigators at the collaborating academic institution (University of Manchester). Main analyses based on published research [26] indicate that data will likely be non-normally distributed, and that therefore, the most appropriate analyses will be Kruskall-Wallis ANOVA and Analyses of Covariance (ANCOVA) at each psychometric assessment time point, in order to compare study groups.

Changes over time in psychometric assessment scores within each group will be conducted using Wilcoxon Signed Ranks Tests—a more conservative significance level of p = 0.001 will be adopted to compensate for the increased risk of Type I errors associated with multiple comparisons. Effect sizes will also be calculated to examine robustness of between-group differences and within-group changes, in addition to examining clinically significant changes over time by analyses of numbers of participants fulfilling clinical threshold scores for substance dependence, depression and anxiety. Regression analyses will be conducted to control for baseline differences between groups in terms of sample size, severity of substance dependence and mental health sequelae, psychosocial functioning and quality of life, as measured by the battery of standardized psychometric assessments. Additionally, mixed effects models will be used to compensate for the independence assumption inherent to regression analyses.

Interim analyses will be performed on the first 30 participants of each group to have completed the three- and six-months follow-up assessments after treatment completion. The data will be subjected to ANOVA and ANCOVA. Changes over time in psychometric assessment scores within each group will be conducted using Wilcoxon Signed Ranks Tests, assuming data are non-normally distributed. If following the interim analysis, a significant difference in outcomes is detected between the groups, either the sample size will be recalculated or recruitment will be discontinued, depending on the statistical power obtained.

Sub-group analyses will be conducted to examine the influence of sociodemographic variables such as age and gender, and clinical characteristics such as primary problem substance and clinically relevant depression and anxiety, on outcomes. Sub-group analyses will be conducted using ANOVA, ANCOVA and regression.

Intention-to-treat (ITT) principles will be followed, with data from all randomised participants being included in these analyses. Mixed effect models will be used to handle missing data by maximum likelihood estimation, which uses all available data from randomised participants and has been demonstrated to minimise bias more effectively than other approaches [46]. A number of strategies will be employed to maximize follow-up and prevent missing data as far as possible. These will include the study team contacting participants directly to chase-up incomplete assessments and working closely with clinical staff to contact those participants who cannot be contacted by the study team directly—reasons for missing data and drop-out will be recorded where this information is available. Additionally, non-randomised, observational, per-protocol comparative analyses will be conducted using data only from participants who fulfilled all protocol requirements in terms of eligibility, intervention receipt, and outcome assessment completion, in order to ascertain effects from BFO under ideal conditions.

Responsibility for data management will lie with the Chief Investigator, and the Principal Investigator within the Sponsor organization. A detailed allocation of responsibilities will be completed by the Chief Investigator as a separate document (‘Delegation Log’), which will be followed by the investigational site personnel and Sponsor personnel. Routine data monitoring for this trial will be completed by the Sponsor Clinical Trial Coordinator, who will conduct monitoring visits on a pre-determined schedule with the site Principal Investigator, other relevant clinicians at site, and trial staff. The Clinical Trial Coordinator will report directly to the Chief Investigator and Sponsor organization. Monitoring and auditing intervals for this study will be based on a risk-assessment undertaken by the Sponsor prior to first participant recruitment and will be appropriately communicated to the study site in advance. The trial will adhere to any routine internal audit processes already in place within the participating organization.

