### Participants

Participants will be service users currently in treatment for SUD who meet the following inclusion criteria: (i) aged 18 years or above, (ii) experiencing problem alcohol and/or drug use for ≥ 12 months requiring treatment, as determined by clinical personnel at the service, (iii) willing to comply with an eight-week treatment program for problem alcohol and/or drug use, (iv) willing to provide outcome measures post-treatment, and at three and six-months follow-up, (v) able to read, write and communicate in the English language, (vi) willing and able to access an internet enabled device for the eight-week treatment period, (vii) willing and able to give informed consent for participation in the study, and capable of understanding and complying with protocol requirements.

Exclusion criteria are as follows: (i) under 18 years of age, (ii) participation in any other alcohol and/or drug related clinical studies within 12 months prior to date of consent, (iii) detention under the Mental Health Act, (iv) clinically significant intellectual or developmental disability which may impair ability to engage with BFO and/or complete the necessary assessment measures included in the methodology, (v) pregnancy (as self-reported), (vi) previous use of BFO to address drug or alcohol use within the past 12-months.

The projected sample size will require 61 evaluable participants in each of the two treatment groups (interventional and control) to achieve enough observed power (assuming an observed power of 0.80 with α = 0.05) with an allowance of 50% attrition at three and six-months follow-up, in order to detect a medium effect size (d ≤ 0.50). Therefore, to obtain a total of 122 evaluable participants, it is estimated that a total of 183 participants will need to be recruited and screened. These estimations have been based on previous alcohol and drug studies size samples [8], some of which have used longitudinal statistical analyses.

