Another potential limitation is the likely attrition rate from a study including individuals with SUD – previous research has demonstrated high levels of attrition in SUD intervention RCTs, especially when the intervention under investigation is digital [47, 48]. Individuals with SUD may have mental health difficulties, financial and accommodation instability, and may experience periods of lapse and relapse; each of these factors may create difficulties when trying to support such individuals to remain engaged with treatment programs [49, 50]. Although the fortnightly recovery check-in phone calls are intended to enhance retention of participants in the BFO arm of the study, it may be more challenging to retain participants in the study once the treatment period is over and they are no longer receiving the check-in phone calls—a prediction supported by previous systematic reviews into smoking cessation interventions [51]. Every attempt will be made to obtain follow-up data—as follow-up data is being collected via electronic methods, there is scope to send reminders to participants to complete follow-up assessments via email, a method indicated to be successful in increasing follow-up retention in previously conducted RCTs [52]. 

Despite the potential limitations of a study such as this, if BFO and the telehealth delivery approach included appear to support individuals to achieve recovery from SUD, findings could inform treatment delivery across SUD services more generally and could increase patient access to support even when in-person services may be restricted or unavailable.

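### The analysis named as principal, and the per-visit tests called most appropriate, cannot meet the protocol's own rule that all randomised participants are included by maximum likelihood.

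*Protocol article*

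**What the plan says.** All of the analysis statements stand in the protocol article, Data analysis and management.

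- Principal method, for primary and secondary outcomes: "The principal data analytical strategy will be a repeated measures analysis of variance (ANOVA".
- Later in the same paragraph, because non-normal data are expected: "the most appropriate analyses will be Kruskall-Wallis ANOVA and Analyses of Covariance (ANCOVA) at each psychometric assessment time point".
- Mixed models first appear after the regression analyses, as an addition: "Additionally, mixed effects models will be used to compensate for the independence assumption inherent to regression analyses".
- Analysis population: "Intention-to-treat (ITT) principles will be followed, with data from all randomised participants being included in these analyses".
- Missing data: "Mixed effect models will be used to handle missing data by maximum likelihood estimation, which uses all available data from randomised participants".
- Software: "Data will be analyzed using SPSS® Version 26.0 (or later").

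The Participants section sets 61 evaluable participants per group and 183 to be recruited, "with an allowance of 50% attrition at three and six-months follow-up". No sentence makes the mixed model the primary analysis. None says how a participant with a missing visit would enter the ANOVA, ANCOVA or Kruskal-Wallis test, and imputation is not mentioned.

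**The concern.** The section gives precedence to one method, says that others suit the expected data better, and then sets an inclusion rule that neither satisfies. If the principal method is followed as named, the headline result compares completers, and randomisation no longer guarantees that completers are comparable between arms. If the inclusion rule is followed instead, the principal method has to be set aside. The text does not say which instruction gives way, so the choice could be made after the results are known. At the attrition the protocol allows for, the two routes analyse very different numbers of people.

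**Working it through.** **1. The plan's own sample size.** Inputs from Participants: d = 0.50, α = 0.05 (two-sided assumed), power 0.80.

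n per arm = 2(1.960 + 0.842)² / 0.50² = 62.8, so 63 (64 by t-test). The stated 61 is close: power at 61 per arm is Φ(0.50·√(61/2) − 1.960) = Φ(0.80) = 0.79, or 0.78 by t-test.

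**2. From evaluable to recruited.** 122 × 1.5 = 183, whereas 122 / (1 − 0.50) = 244. Going from 183 to 122 is a loss of 61/183 = one third. The stated 50% and the implied one third disagree. That is a separate matter, so both are carried forward.

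**3. What each named method does with a missing visit.** This is how the standard methods behave; the article does not state it.

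| Method | Who is analysed | Meets the inclusion rule? |
|---|---|---|
| Repeated measures ANOVA | complete at every visit | no |
| Kruskal-Wallis at a visit | observed at that visit | no |
| ANCOVA at a visit | observed at that visit, with baseline | no |
| Mixed model, maximum likelihood | all available data | yes |

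**4. Numbers left for the ANOVA if 183 are randomised.** Power is for a two-group t-test at one time point with d = 0.50.

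- 50% loss: 183 × 0.50 = 91.5, about 92 in total (45.75 per arm); power about 0.66.
- One-third loss: 183 × 2/3 = 122 (61 per arm); power about 0.78.

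These are upper limits for the ANOVA, because missing any earlier visit also removes a participant.

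**5. Bias, by illustrative simulation.** Assumptions, none taken from the documents: no true effect, 92 per arm, correlation 0.6 between all visits, 50% dropout after week 8 in both arms, and 5% two-sided tests. In the first scenario dropout depends on week-8 use in controls only, at log-odds 1 per SD.

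| Analysis of completers | Bias (SD) | Rejection |
|---|---|---|
| Unadjusted six-month comparison | 0.25 | about 22% |
| Baseline-adjusted ANCOVA at six months | about 0.1 | about 10% |
| Repeated measures ANOVA, group-by-time | – | about 13% |

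An estimate that conditions on baseline and week 8, as a likelihood analysis does, has bias of about 0.

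Other dropout mechanisms:

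- Controls only, log-odds 0.7: unadjusted difference 0.19 SD, rejection 13–14%.
- Controls only, log-odds 0.5: 0.15 SD, about 10%.
- Log-odds 1 in controls and 0.5 in the other arm: rejection about 8% unadjusted, 6% for ANCOVA.
- Same mechanism in both arms: no bias, rejection about 5–6%.

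A second simulation had a true effect of −0.50 SD and dropout depending on the last observed value. With outcome-related dropout in one arm only (log-odds 0.7), completers gave −0.23 to −0.30 or −0.70 to −0.78, depending on which arm was affected. Maximum likelihood stayed at about −0.50.

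**The case against.** The strongest reply is that the plan already contains a method that keeps everyone. The paragraph on methods can be read as an intended analysis with a fallback for skewed data, and the mixed model as the missing-data rule, not a third rival. That stands in part: what is absent is a statement of precedence, not a missing-data method. It does not remove the conflict. The text does not say that the repeated measures analysis is to be run as a mixed model, and that reading could not cover Kruskal-Wallis or per-visit ANCOVA.

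A reader might also infer more than the article supports:

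- *That the protocol expects retention to differ between arms.* The Discussion says "the fortnightly recovery check-in phone calls are intended to enhance retention of participants in the BFO arm of the study", but goes on to warn that retention may become harder after treatment, when the calls have stopped. That is an aim during treatment, not a forecast of a difference at follow-up.
- *That 22% is the error rate of the principal analysis.* It belongs to an unadjusted six-month test under one assumed mechanism. The ANOVA group-by-time test gives about 13% there. Its group main effect does worse (about 40%), but group-by-time is the usual test of a longitudinal effect, and completers' change from baseline to six months shows bias of about 0.
- *That half the sample will be lost.* The 50% is an allowance, the recruitment figure implies one third, and the 183 are described as recruited and screened, not as randomised.
- *That the plan is deficient for not stating a covariance structure, bootstrap errors, an ordinal model or a tipping-point analysis.* Those are matters for the statistical analysis plan, which is not shown, or of preference.

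**Conclusion.** The point holds as a conflict between statements in one section. The principal analysis and the per-visit tests preferred to it cannot, in standard form, follow the article's inclusion and missing-data rule. A statistical analysis plan could add detail, but the protocol has already fixed a principal method that contradicts that rule.

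The size depends on attrition. The ANOVA would use about 92 of 183 at the 50% allowance, or 122 at one-third loss, assuming that 183 are randomised. Whether the completer result is also biased depends on the dropout mechanism, which the documents do not give. There is no bias if dropout works the same way in both arms, and appreciable bias if it relates to outcome in one arm only. The simulated figures show that range and do not predict this trial's error rate. The advantage of the likelihood analysis rests on dropout being explained by observed data.

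**What to change.** Name one primary analysis: the maximum-likelihood mixed model already planned, on all randomised participants, with arm, time, arm-by-time and the baseline value. Report the between-arm contrast with its 95% confidence interval at one stated time point. Label repeated measures ANOVA, per-visit ANCOVA and Kruskal-Wallis as supportive, and say that each uses only participants with the visits it needs. State whether baseline enters as a covariate or as the first repeated measurement, since only the latter keeps participants who have no later visit.

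The cost is a few sentences in the protocol and analysis plan. The model is already in the plan, can be fitted in the named software, and needs no new data.
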